## Methods and Study Research Design

INNOVATE-VSG is a randomized, single-blind, parallel-design clinical trial with a 12-month follow-up, anticipated to enroll patients at two sites. A total of 44 subjects with BMI of 35–50 kg/m^2^, meeting eligibility for bariatric surgery, and having concomitant pathologic GERD (defined as acid exposure time [AET] of ≥ 4.9% as assessed by the Bravo pH study) will be assigned in 1:1 ratio to cVSG or *fvp*VSG. Recruitment is competitive, i.e., one site may recruit more patients than the other. Only the surgeons and the statistician will be unblinded to the randomized treatment assignment; others including the staff performing mechanistic assessments will remain blinded throughout the trial. As is the standard practice at both sites, the patients will have pre- and post-surgery assessments and non-surgical ancillary interventions including diet and lifestyle counseling.

The primary aim is to determine whether *fvp*VSG will be associated with lower acid exposure to the esophagus as assessed by the change in the total AET% at month 6–9 relative to AET% at baseline, as assessed by the Bravo pH study.

To elucidate the mechanistic basis for the primary aim, the following tests will be performed pre-operatively and 6–9 months post-surgery: (1) high-resolution esophageal manometry (HREM) [18] to assess the LES pressure and intragastric pressure; (2) impedance planimetry (EndoFLIP) [19] to assess changes in the gastroesophageal junction compliance; and (3) assess the length of the flap valve via the retroflex view on endoscopic examination at follow-up [18, 19]. Additionally, the resected stomach specimen will be examined for the presence of gastric sling fibers. The impact of change in GERD symptoms on quality of life (QoL) will be examined with two validated rating scales—GERD-HRQL and SF-36 [20, 21]. Body weight and serum metabolic panel (standard testing for bariatric surgery patients) will also be assessed pre-operatively and at 12-month follow-up. All inclusion and exclusion criteria are listed on Table 1.

**Table 1 Tab1:** Study inclusion and exclusion criteria

Inclusion criteria	Exclusion criteria

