1. Male and female subjects aged 18–60 years 2. BMI 35–50 kg/m^2^ 3. Must meet the BMI criteria before and after 6 months of nonsurgical weight management 4. Presence of abnormal acid exposure time (AET) of 4.9% or above as assessed with the Bravo pH test 5. Have health insurance which pays for the costs of bariatric surgery and standard medical care before and after surgery 6. Women of childbearing potential must be using appropriate contraception to avoid pregnancy throughout the study 7. Must be able to provide written informed consent	1. Hiatal hernia > 2 cm 2. Evidence of significant major esophageal motility disorder 3. Severe gastroparesis 4. Previous bariatric or anti-reflux procedure 5. Barrett’s esophagus 6. Subjects requiring mesh treatment at time of procedure 7. Severe heart/lung disease (e.g., heart failure, unstable coronary artery disease, end-stage lung disease) 8. Subjects with pacemakers, implantable defibrillators, neurostimulators 9. Portal hypertension or cirrhosis 10. Chronic pancreatitis 11. Active cancer treatment 12. Inability to tolerate general anesthesia 13. Uncontrollable coagulopathy 14. Significant and uncontrolled inflammatory bowel disease 15. Severe and/or uncontrolled psychiatric disorder 16. Suicidal ideation or unstable/untreated major depressive disorder within the past year 17. Alcohol or substance use disorder within the past year 18. Pregnant, breastfeeding or plan pregnancy in the coming 24 months 19. Diminished intellectual capacity to consent or follow pre- and post-surgery instructions 20. History of, or any current health condition that would make the subject ineligible for sleeve gastrectomy, or put the subject at risk by participation in the study

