### Statistical Analysis

Primary and secondary analyses will be performed using an intent-to-treat (ITT) protocol (i.e., all randomized subjects). Additional sensitivity analyses using modified ITT protocols will be implemented with adjustment for missing data. Per-Protocol analysis will also be conducted to test intervention effect under optimal conditions. The primary efficacy outcome (also used for power analysis) is the change in AET% at month 6–9 relative to AET% at baseline which will be analyzed using an analysis of covariance (ANCOVA) model with fixed effects for treatment group, age, sex, race, baseline weight, and baseline AET%. Secondary analyses will include (1) HREM measures and (2) EndoFLIP measures. Additional analyses will include, but are not limited to, GerdQ score, proportions of subjects with GERD improvement or remission, proportions of subjects with *de*
*novo* GERD, proportions of subjects with worsening of GERD based on symptom score, proportions of subjects with shifts in AET% categories, DeMeester score, quality of life measures (GERD-HRQL, SF-36), and percent weight loss. Dichotomous outcomes will be analyzed using a generalized linear model (GLM), specifically, a log-binomial regression model with fixed effects for treatment, strata, and covariates described above. For each between-treatment group comparison of interest, the estimated risk ratio (relative risk), standard error, 95% Wald confidence interval, and *p*-value will be presented. Logistic regression models will also be explored to generate odds ratios to allow for comparability to existing literature regarding efficacy of pharmacologic interventions. The weight loss measure as a continuous variable will be analyzed using linear mixed models (LMM). All secondary and exploratory outcomes will be analyzed using similar models described above (ANCOVA, GLM, and LMM) under the ITT, modified ITT, and per-protocol procedures.

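### Symptom-defined yes/no outcomes are adjusted for baseline acid exposure but not for the baseline symptom score

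*Protocol article*

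**What the plan says.** All references are to the protocol article. Its Statistical Analysis section gives one covariate list, in the ANCOVA for the primary outcome (change in AET%): "fixed effects for treatment group, age, sex, race, baseline weight, and baseline AET"%. For that outcome, baseline AET% is the outcome's own baseline.

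The section then lists additional outcomes. One is tied explicitly to symptoms: "proportions of subjects with worsening of GERD based on symptom score". The proportions with GERD improvement or remission and with de novo GERD are also listed, without stating whether symptoms or AET define them. For all dichotomous outcomes the model is "a log-binomial regression model with fixed effects for treatment, strata, and covariates described above".

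For the remaining outcomes the text is looser: "All secondary and exploratory outcomes will be analyzed using similar models described above (ANCOVA, GLM, and LMM").

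Table 1 sets the reflux criterion for entry as "Presence of abnormal acid exposure time (AET) of 4.9% or above as assessed with the Bravo pH test". None of the seven inclusion criteria asks for symptoms or a minimum questionnaire score.

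**The concern.** A list built for AET% has been carried over to outcomes that are not about AET%. In the primary model, baseline AET% does what a baseline covariate should do. In a model for worsening on a symptom score, the corresponding covariate is the symptom score before surgery, and the specified model leaves it out.

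The omission matters because a change category on a bounded scale depends on the starting point. A patient who enters with a score at the floor cannot improve on it. A patient near the top has little room to worsen. Because entry rests on acid exposure alone, both kinds of patient are eligible. If by chance one arm starts with more low-symptom patients, part of the difference in the proportion worsened may reflect that start and not the operation. The Discussion in the abstract says that the data will be used to design a larger multi-center trial, so these proportions may be reused.

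**Working it through.** **Inputs**
- Sample size: "A total of 44 subjects" (Methods and Study Research Design).
- Allocation: "assigned in 1:1 ratio to cVSG or" fvpVSG, hence 44/2 = 22 per arm.
- Covariates fixed for dichotomous outcomes: treatment, strata, age, sex, race, baseline weight, baseline AET% (Statistical Analysis).
- Symptom requirement at entry: none (Table 1).

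The article states no figure for the precision of any dichotomous outcome, so there is none to reproduce.

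**Step 1: does the specified model contain the baseline symptom score?** The sentence on dichotomous outcomes refers back to the covariates already described. Only one list precedes it, and no questionnaire score is on it. The sentence positively specifies the covariates, so this is more than detail left to another document.

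**Step 2: which outcomes are affected?**
- Worsening by symptom score: affected, since the article ties it to symptoms.
- Improvement or remission: affected only if defined by symptoms. If defined by AET, baseline AET% is the right baseline.
- De novo GERD: affected if defined by symptoms. Every entrant already has pathologic GERD by AET, so a symptom definition is the likelier reading, but this is an inference.

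**Step 3: how large can chance imbalance be?** In units of the standard deviation (SD) of a baseline measure, the difference between two arm means has standard deviation

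sqrt(1/22 + 1/22) = sqrt(2/22) = 0.30.

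Under a normal approximation:
- P(absolute difference > 0.3 SD) = 2 × [1 − Φ(0.3/0.3015)] = 0.32
- P(absolute difference > 0.5 SD) = 2 × [1 − Φ(0.5/0.3015)] = 0.10

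So there is about a one-in-three chance that the arms differ by more than 0.3 SD in baseline symptom score, and a one-in-ten chance of more than 0.5 SD.

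**Step 4: what does that do to the risk ratio?** This would need the distribution of baseline scores, the cut-off that defines worsening, and the relation between baseline score and category. The article gives none of these, so the effect on the log-binomial estimate cannot be computed.

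**Step 5: is there room for another term?** Counting one coefficient each for treatment, age, sex, race, baseline weight and baseline AET%, and at least one for strata, the model has at least 7 coefficients plus an intercept in 44 patients, or at most 44/7 = 6.3 patients per coefficient. Log-binomial models can fail to converge in such conditions. This favours replacing baseline AET% over adding a term.

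**The case against.** **The continuous outcomes.** A reader might infer that manometry, EndoFLIP and questionnaire scores are also analyzed without their own baselines. The document does not support that. For these it promises only similar models, and the ANCOVA it describes adjusts AET% change for baseline AET%. The natural counterpart for LES pressure change adjusts for baseline LES pressure. The text is unspecific here and does not show an omission, and a per-outcome list may sit in the analysis plan. What stands is a request to confirm.

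**Power.** A reader might attach a loss of power to the point. For a continuous change score not adjusted for its own baseline, with a covariate unrelated to it, efficiency relative to ANCOVA is (1 + r)/2. Assumed baseline/follow-up correlations r of 0.3, 0.5 and 0.7 give 44 × (1 + r)/2 = 28.6, 33.0 and 37.4 equivalent patients. These figures concern continuous change scores under assumed correlations. They do not carry over to a log-binomial model, which is the only place where the text fixes the covariates.

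**Floor effects.** Symptom-free entry creates a floor on symptom scales, not for LES pressure or compliance. A patient with few symptoms can still improve somewhat, and baseline adjustment does not remove a floor. The article does not say how many entrants would be near it. Nor can one say that low-symptom patients dilute the improvement or remission proportion, because that outcome is not stated to be symptom-based.

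**Bias.** Randomization keeps the comparison unbiased on average, and the standard error allows for chance imbalance. That is correct. The point concerns precision and imbalance in the one sample obtained.

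**Stakes.** The affected outcomes are among the additional analyses of a pilot, and the primary ANCOVA does adjust for its own baseline. Also correct, and it limits the weight of the point.

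**Conclusion.** The point holds for symptom-defined dichotomous outcomes: with certainty for worsening by symptom score, and for improvement or remission and de novo GERD if these are defined by symptoms. The specified model adjusts for acid exposure and omits the more relevant baseline. The cost is lost precision and exposure to a chance baseline difference whose standard deviation is 0.30 SD at 22 per arm. That figure assumes all 44 patients are analyzed in equal arms. The effect on the risk ratios cannot be sized from the document.

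For the continuous outcomes there is an ambiguity to settle, not an error. The primary analysis is not affected. This is a free improvement and does not threaten the trial's main conclusion.

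**What to change.** 1. In the models for symptom-defined dichotomous outcomes, replace baseline AET% with the baseline score of the questionnaire that defines the outcome. Replace, do not add, for the convergence reason given above.
2. State for improvement or remission and for de novo GERD whether symptoms or AET define them, so that the matching baseline follows.
3. Confirm in one sentence that the similar ANCOVA for each continuous outcome measured before surgery (LES pressure, EndoFLIP compliance, GerdQ, GERD-HRQL, SF-36, DeMeester score) uses that outcome's own baseline in place of baseline AET%.

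The cost is wording, settled before the data are analyzed. No new measurement should be needed. For manometry and EndoFLIP the article says that "the following tests will be performed pre-operatively and 6–9 months post-surgery", and the questionnaire endpoints are defined as changes, which requires a score before surgery. The number of model terms stays the same.

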## Discussion

Sleeve gastrectomy is the most frequently performed bariatric operation in the world. This operation is associated with significant weight loss and improvement/resolution of comorbidities. However, there is one side effect that continues to plague this operation, i.e., persistent or de novo GERD. The GERD symptoms can worsen after sleeve gastrectomy and a proportion of patients develop new onset GERD symptoms following surgery. Considering our knowledge of the antireflux barrier, we propose that GERD after sleeve gastrectomy is due to the anatomic disruption of the native antireflux barrier. Specifically, the cVSG transect the gastric fundus at the level of the angle of His, which disrupts the native oblique entry of the esophagus to a direct entry path into the stomach, thus eliminating the naturally-occurring gastroesophageal valve. The proposed *fvp*VSG is a technical variant of the cVSG; it maintains the weight loss function of a bariatric operation while strengthening the antireflux barrier at the same time. Our findings could have an impact of reducing the prevalence of GERD following VSG.

## Trial Status

This trial is anticipated to open in February 2025.

## Data Availability

No datasets were generated or analysed during the current study.
